#### Secondary outcomes

To assess correlation of specific MDR-TB drug serum concentrations with observed adherence, bedaquiline and linezolid pre-dose concentrations (C_trough_) will be used. To cater for those who may be adherent but have low bedaquiline or linezolid concentrations, we will use of cut-off value of bedaquiline C_trough_ from previous studies, below which a participant will be classified as non-adherence. Linezolid will be used to assess more recent adherence than bedaquiline.

We will compare time to sputum culture conversion in the intervention and control arm using time to event analysis. We shall also use chi-square testing to compare treatment success rates in the intervention and control arms. Treatment success will be evaluated using a composite outcome that includes TB cure (for microbiologically diagnosed patients) and TB treatment completion (for clinically diagnosed TB). We will undertake per-protocol and intention to treat analyses to compare TB cure rates in the two study arms. We will determine the proportions of patients retained in care of retention in care at 2 and 6 months in the two study arms using chi-square tests. Study outcomes by randomization arm will be compared using a generalized estimating equations (GEE) model using repeated measures with identity link, exchangeable correlation structure and robust variance estimates. Adjusted coefficients along with their corresponding 95% CIs will be generated. Statistical significance will be set at the *P* < .05 level and statistical analyses performed using Stata version 14 (StataCorp, College Station, TX, USA).

#### Additional analyses and handling of missing data

Interim data analysis will be conducted once 50% of the overall sample size has been achieved with the purpose of guiding the data monitoring board on recommendations for the study. Missing data will be dealt with as missing covariate and outcome data. As a generalized estimating equations model will be used, missing outcome data will be dealt with using a missing at random assumption. If > 3% of data for covariate data is missing, multiple imputation will be used for the primary analysis. Given the way the adherence rate is computed, we anticipate that there may be a number of ways that the outcome measure could be missing. These include loss to follow-up and or partial information collected at anyone study visit. A further analysis will be performed in which missing primary outcome data will be imputed. Multiple imputation will be also performed on missing covariate and outcome data for all secondary clinical analyses in a similar way to that performed for the primary analysis.

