#### Intervention arm

For this trial, we shall use two kinds of MEMS-operated devices, the MEMS cap and the MEMS Electronic DosePak® (EDP). At enrolment, patients on the self-administering arm will be provided with both devices; the MEMS cap will be placed over a medicine bottle containing bedaquiline. The concomitant medication will be packaged in a convenient pack containing all tablets to be swallowed each day and placed into the medication box with the EDP® technology Patients will be instructed on how to use the MEMS devices. Each time a patient opens up the cap over the bedaquiline bottle or the lid of the medicine box, the time and date of this event will be immediately captured. Adherence data from the MEMS devices will be downloaded by the study team every month during the routine visits. The devices will provide information on specific calendar dates and times when the devices were opened. Information on the calendar days with event markings to signify the date and time when medication containers were opened will be displayed on a computer. The software will contain two separate input calendars for both the MEMS cap and the EDP box for each participant. This same adherence data will be shared with primary clinician and used to tailor adherence counselling given to patients, exploring patterns of missed medication and brainstorming for solutions with the patient (Table 1).

**Table 1 Tab1:** Description of study arms

**Control: DOT**	**Intervention: self-administered therapy with MEMS technology**
Patients report daily to the nearest health unit to be observed by a health care provider as they ingest their medication Behavioural: Adherence counselling. Patients will receive adherence counselling as scheduled by their primary care health providers	Device: MEMS CAP without LCD display and EDP® technology on medicine box. Standard MEMS devices record the time and date when the bottle is opened The MEMS technology automatically complies drug dosing history information by electronically recording the date and time of each opening of the medication cap and or box Behavioural: Adherence counselling. Patients will receive adherence counselling as scheduled by their primary care health providers

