### Determination of TB treatment outcomes

At the end of therapy treatment (9 months for participants that qualify for shorter MDR-TB/RR-TB treatment regimen and 18 months for those selected for the longer MDR-TB/RR-TB treatment regimen), clinical and laboratory information is routinely compiled by each MDR-TB centre and forwarded to the National TB Program (NTP) review committee for discussion on consensus on treatment outcome based on a specified criterion (Table 2). TB treatment outcomes for this study will be as determined by the review committee.

**Table 2 Tab2:** Description of MDR-TB treatment outcomes

**Outcome**	**Definition**
Time to culture conversion	Time from initiation of treatment to the time point where the patient has two consecutive negative cultures
Cured	1. A patient who has culture converted and 2. Received treatment for a total duration of 9–11 months and 3. Has at least 3 consecutive negative TB cultures at least 30 days apart and 4. No evidence of clinical deterioration
Treatment completed (success)	1. A patient who has culture converted and 2. Received treatment for a total duration of 9–11 months and 3. Has less than 3 consecutive negative TB cultures at least 30 days apart and 4. No evidence of clinical deterioration
Loss to follow-up	A patient with treatment interrupted for 2 consecutive months and more
Treatment failure	1. A patient who failed to culture convert by month 5 (shorter regimen) or month 6 (longer regimen) or 2. In the initial 6 months of treatment more than 2 of 5 cultures are positive or 3. Treatment stopped due to adverse events 4. Permanent discontinuation of two Group A drugs (BDQ, LZD, or LFX) in the first 6 months of the modified shorter regimen or 5. More than 2 new drugs added because of poor clinical response or 6. Panel decision to terminate any further DR-TB treatment
Died	A patient who died for any reason during treatment

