#### Control arm

Patients randomized to the control arm will receive daily DOT provided by a peripheral health facility close to their residence. Under the DOT programme, patients report to the nearest DOT provider facility daily and drug intake is observed. On each visit, the TB card is ticked off in correspondence with the number of days they made a visit to the health centre and this card is retained at the health facility. At the monthly visits, the TB card is taken to the central MDR treatment facility for review by the managing clinician. At this point, the study team will record the number of doses taken/missed according to the TB card. Participants will receive adherence counselling on all routine visits at the central facility (Table 1).

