### Statistical: outcomes

#### Adherence assessment

The primary outcome is the overall adherence rates among MDR-TB patients on self-administered therapy and on DOT. For the participants on the intervention arm, opening of the devices will be equated to a patient swallowing their medication and adherence will be derived from the number of days the device was opened as a proportion of the total number of days in the entire period of their MDR-TB treatment. Patients on the intervention arm will be required to take no less than 70% of their medication to be considered as having good adherence. For participants on the control arm (DOT), adherence information will be obtained from their TB treatment cards. Adherence rates will be calculated from the number of days that they report to the DOTS facility as a proportion of the total number of treatment complaint days in the entire period of their MDR-TB treatment. Participants who take their medication at least 80% of the time (missing no more than 5 days each month) will be considered as having good adherence.

The primary analysis will be a comparison of overall adherence in each arm. Adherence by self-administration (proportion of expected openings of the MEMS devices) and DOT (proportion of DOT visits) will also be compared at 2 months and 6 months in the intervention and control arms. The chi-square test and 1-way analysis of variance models will be used to compare outcomes by randomization arm. We shall use independent samples *t*-test to test for statistical difference mean adherence rates in the patient in the intervention and control arms. We will use an intent-to-treat approach (analysed all participants regardless of drug refills) to compare adherence outcomes by randomization arm using a generalized estimating equations model using repeated measures with identity link, exchangeable correlation structure and robust variance estimates.

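### Loss to follow-up, which Table 2 defines as interrupted treatment, is handled as adherence data missing at random, and the use of GEE does not justify that

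*Protocol article*

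**What the plan says.** Under Additional analyses and handling of missing data, the protocol article says: "As a generalized estimating equations model will be used, missing outcome data will be dealt with using a missing at random assumption". On how the adherence outcome may come to be missing, it adds: "These include loss to follow-up and or partial information collected at anyone study visit". It also plans a second look: "A further analysis will be performed in which missing primary outcome data will be imputed". No departure from missing at random is described for that analysis.

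The model, under Adherence assessment, is a "generalized estimating equations model using repeated measures with identity link, exchangeable correlation structure and robust variance estimates". No weighting is mentioned.

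Table 2, under Determination of TB treatment outcomes, defines loss to follow-up as "A patient with treatment interrupted for 2 consecutive months and more".

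For the self-administered arm, adherence is the "number of days the device was opened as a proportion of the total number of days in the entire period of their MDR-TB treatment". For the DOT arm, the denominator is the number of treatment complaint days (presumably compliant days) over the treatment period.

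On data capture, the Intervention arm section says: "Adherence data from the MEMS devices will be downloaded by the study team every month during the routine visits". In the Control arm section, "the TB card is ticked off in correspondence with the number of days they made a visit to the health centre"; the card stays at the facility and is taken to the central centre for the monthly visit, where the study team records doses taken and missed.

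**The concern.** The primary outcome is the share of treatment days on which drug was taken. A patient lost to follow-up in the sense of Table 2 has at least two months with none taken. That is close to the worst value the outcome can have, but the missing-data section classes it as an absent value and assumes it can be predicted from what was observed.

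The reason given is also wrong. Choosing a GEE does not bring validity under missing at random. Unweighted GEE is in general valid only if missingness is completely at random or depends only on covariates in the model.

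The article is also at odds with itself. The adherence definition for the self-administered arm, over the entire treatment period, can be read as counting lost days as days not taken. The missing-data section treats the same loss as missing.

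The trial asks whether daily observation can be dropped without losing adherence. If patients stop treatment more often in one arm, that difference is what the trial must detect, and this rule can remove it from the primary estimate.

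**Working it through.** The plan gives no figure for the effect of this rule, so there is none to reproduce.

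**Inputs from the protocol article (Sample size):** 20% loss to follow-up; non-inferiority margin of −10 points for MEMS minus DOT, judged on the lower limit of the 95% CI.

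**Assumptions, not in the article:** adherence while on treatment a = 80%; none after loss; loss one half or one third of the way through, so the share of the period lost is s = 1/2 or 2/3; any split of loss between arms.

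**1. One arm.** With a fraction f lost, the true mean is a(1 − f·s). If lost months are left out, the model returns about a. The overstatement is a·f·s.
- s = 1/2: true mean 0.8×80 + 0.2×40 = 72.0; modelled 80; overstated by 8.0 points.
- s = 2/3: true mean 0.8×80 + 0.2×26.7 = 69.3; modelled 80; overstated by 10.7 points.
- Range at a = 85%: for s from 25% to 75%, 4.3 to 12.8 points with 20% lost and 2.1 to 6.4 points with 10% lost.
- If patients kept taking half as much (40%) after loss, the s = 1/2 figure falls to (80 − 40)×0.2×0.5 = 4.0 points.

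**2. Difference between arms, same recording.** The bias in MEMS minus DOT is a·s·(f_MEMS − f_DOT).
- Equal loss: 0.
- 30% versus 10% (20% overall): at s = 1/2 the true means are 0.7×80 + 0.3×40 = 68.0 and 0.9×80 + 0.1×40 = 76.0, a difference of −8.0. At s = 2/3 they are 64.0 and 74.7, a difference of −10.7. The model returns about 0 in both cases.
- 25% versus 15%: bias 80×0.5×0.1 = 4.0 or 80×(2/3)×0.1 = 5.3 points.
- If DOT loses more patients, the sign reverses.

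**3. Difference between arms, unequal recording.** With 20% lost in each arm, suppose absence is scored as missed doses in one arm and left missing in the other. The false difference is the one-arm overstatement, 8.0 to 10.7 points, in favour of the arm whose absences are left missing.

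**4. Check by simulation.** Set-up: 150 trials per scenario, 82 per arm, nine monthly values, unweighted exchangeable GEE, 85% adherence while followed, half the period lost on average.
- Equal loss and recording: bias about 0.
- 30% versus 10% loss: true difference about −7.6, GEE 0.0.
- Equal loss with only DOT absence counted as missed: true difference about 0, GEE about +7.7.

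The closed form at 85% gives 85×0.5×0.2 = 8.5 for the last two, so the simulation is of the same order.

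**5. GEE when data really are missing at random.** In one test with 36% lost and a true mean of 80.2%, an exchangeable GEE gave 80.0% and an independence GEE 82.0%. The error from the GEE argument was therefore small for the specified exchangeable structure in that test. The larger problem is that interruption is not missing at random.

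**The case against.** The strongest reply is that two meanings of loss to follow-up are being merged. Table 2 gives a treatment outcome decided by the national programme's review committee. The sample-size allowance and the missing-data section may mean attrition from the study, where adherence is truly unknown. The article does not say which, and this stands as a caution: not all of the 20% need be interruption with zero adherence. It does not rescue the rule, because the only definition in the article is interruption and nothing exempts those patients from the missing-at-random handling.

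Second, with equal loss and equal recording the tested difference is unbiased. That stands in full.

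Third, the article has partial safeguards: analysis of all participants regardless of refills, the imputation analysis, and loss to follow-up and retention reported by arm. A large imbalance would therefore be visible. These safeguards do not correct the primary estimate, and imputation under the same assumption would again borrow from patients still followed.

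A reader might infer that the bias must favour MEMS, since a patient who stays away brings no download while the DOT card shows unticked days. The article does not establish this. The card also reaches the study team through the monthly visit. Background and rationale says the device can send data in real time and store them for many months. The DOT denominator could drop interrupted days and flatter DOT instead. It would also be wrong to say that GEE fills in doses: it imputes nothing, and simply uses the observed months.

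Finally, weighting details and sensitivity ranges commonly belong in an analysis plan. Their absence is not the fault here; the stated rule and its stated reason are.

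**Conclusion.** The point holds as a defect in what the protocol article states. Loss defined as interrupted treatment is classed as missing at random, on a justification that is not correct in general for an unweighted GEE, and this conflicts with a whole-period reading of the adherence definition.

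At 20% loss, 80% adherence on treatment and none afterwards, each arm's mean is overstated by about 8 to 10.7 points. Bias in the difference needs unequal loss or unequal recording. An assumed 30% versus 10% loss would turn a true −8 to −10.7 into about 0. The first figure uses four fifths of the margin and the second exceeds it. Only the 20% and the −10 come from the article; the rest are scenarios. The document does not show that loss will be unequal, nor which arm unequal recording would favour. That uncertainty is a reason to fix one common rule before outcomes are compared by arm.

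**What to change.** - In the primary analysis, count every prescribed day after treatment interruption or loss, while the patient is alive and treatment has not been stopped by a clinician, as not taken. Use the same denominator of prescribed days in both arms.
- Reconcile Adherence assessment with Additional analyses and handling of missing data accordingly, and say whether loss to follow-up there has its Table 2 meaning.
- Reserve missing-data methods for true data failures, such as a device fault or a lost card. Multiple imputation by arm, a weighted GEE or a mixed model would serve.
- Delete the statement that using GEE justifies missing at random.
- Add a missing-not-at-random sensitivity analysis (delta or tipping-point), read against the −10 point margin.

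The cost is revised wording and a little more analysis. Reported adherence will be lower in both arms.

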## Monitoring

### Data monitoring: formal committee

The independent Data Monitoring Board (DMB) will make recommendations concerning the study to the Trial Steering Committee. The DMB is chaired by [name] Senior Lecturer, in the Department of Epidemiology & Biostatistics at Makerere University School of Public Health in the College of Health Sciences, and other members include [name], a review Coordinator for Centre for Systematic Reviews on Human Resources for Health; [name], National MDR-TB Coordinator at the NTP; and [name], a lecturer in the Department of Community Health and Behavioural Sciences, Makerere University. The DMB is independent from the sponsor and has no competing interests.

### Data monitoring: Interim analysis

The first interim analysis will be conducted when 50% of the participants complete the study medication. Trial monitoring is conducted independent of the investigators by internal monitors at the Infectious Diseases Institute. The Trial Steering Committee is composed of [name], program manager at the NTP in Uganda; [name], Nurse in charge at Lira Regional Referral Hospital; [name], a senior statistician with experience in HIV clinical trials and cohort studies; and [name], a lay representative from the Friends’ Council (patient group) at the Infectious Disease Institute, Uganda. Since this trial is unblinded, the DMB will have access to intervention assignment. They will ensure that we protect the safety of the participants while assuring study integrity. The DMB will periodically (every 6 months) review the data, including interim analyses, and communicate any concerns to the study team and TSC.

### Harms

All observed or volunteered adverse events (AEs) regardless of treatment group or suspected causal relationship will be reported. During each study visit, the study doctors will assess AEs that may have occurred since the previous visit. The severity of adverse events will be graded according to the National Institute of Health Division of AIDS (DAIDS) classification system for reporting adverse experiences in adults [16].

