**Methods:**

We plan to enrol 164 newly diagnosed MDR-TB patients aged ≥ 8 years from three regional hospitals based in rural and urban Uganda. Patients with conditions that affect their dexterity and ability to operate the MEMS-operated medicine equipment will not be eligible to participate in the trial. Patients are randomized to either of the two study arms: self-administered therapy with adherence being monitored using MEMS technology (intervention arm) or health facility-based DOT (control arm) and will be followed up monthly. Adherence is measured by the number of days the medicine bottle is open to access medication as recorded by the MEMS software in the intervention arm and treatment complaint days as recorded in the TB treatment card in the control arm. The primary outcome is the comparison of adherence rates between the two study arms.

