#### Eligibility criteria

We shall enrol consented patients with newly diagnosed pulmonary MDR-TB and RR-TB patients aged ≥8 years, initiated on oral MDR-TB therapy (category 1 or 2). Patients with any condition that inhibits the use of the MEMS device, e.g. dexterity or debilitating arthritis, will be excluded from participation.

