### Adherence to interventions

Participants on the intervention arm will be given monthly study visits in which the adherence software shall be read to determine information on use of the medicine cap and box. Based on the information displayed, study personnel provide tailored adherence counselling to the participants. For participants below the age of 18 and under guardianship, their caretakers will be included in the adherence counseling sessions.

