#### Randomization and allocation of intervention

Blinded randomization will be performed by the study team (medical officer or study nurse) at the time of enrolment using an automated randomization sequence within the Redcap data capture tool. The randomization will be done in real time on the Redcap tool as it will be Internet enabled. Participants will be randomized to either intervention arm (arm 1; self-administered therapy) or control arm (arm 2; DOT). Stratified randomization will be performed according to age group and gender. Due to the nature of the intervention and organization of patient care, it will not be possible to blind either participants or study staff to the study arm allocation

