### Ethical considerations

The study has received approvals from the Mulago Hospital Research and Ethics Committee (Ref No: MHREC2125), the Uganda National Council for Science and Technology (Ref No: HS1796ES) and the National Drug Authority (RefNo:476/NDA/DPS/08/2021). The informed consent/assent document are in compliance with GCP and local regulatory authorities. Participants are taken through the consent process by the study team (Medical Officer or Study Nurse). Assent is requested from children between 8 and 17 years, and in addition, consent is sought from their parents or legally authorized representative. Informed consent is sought from participants aged 18 years and above and emancipated minors. Approval for protocol amendments shall be submitted to the Mulago Hospital Research and Ethics Committee for approval and then communicated to the National Drug Authority and The Uganda National Council for Science and Technology before implementation. Participants will be free to withdraw at any point of the study without any compromise to receiving their standard therapy. Children aged 8–17 years that do not provide assent but whose guardians have signed consent or vice versa will not be included in the study.

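### The only adverse event severity standard stated is described as one for adults, although the trial enrols from age 8, so the grading that applies under 18 needs to be settled

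*Protocol article*

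**What the plan says.** The Harms section sets the scope of safety reporting without any age limit: "All observed or volunteered adverse events (AEs) regardless of treatment group or suspected causal relationship will be reported". Study doctors assess events at each visit, and severity is graded with the "Division of AIDS (DAIDS) classification system for reporting adverse experiences in adults". No second scale is named.

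Four other places show that minors are a planned part of the trial:

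- Abstract, Methods: "We plan to enrol 164 newly diagnosed MDR-TB patients aged ≥ 8 years".
- Eligibility criteria: "newly diagnosed pulmonary MDR-TB and RR-TB patients aged ≥8 years".
- Adherence to interventions: "For participants below the age of 18 and under guardianship, their caretakers will be included in the adherence counseling sessions".
- Ethical considerations: "Assent is requested from children between 8 and 17 years", with consent from a parent or legal representative as well.

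Randomization also uses age: "Stratified randomization will be performed according to age group and gender". The age cut-offs are not given.

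**The concern.** A severity grade has meaning only relative to the population for which its criteria were written. Here the article says that those criteria are for adults and then applies them to everyone, including children from age 8. A site doctor who follows the Harms section literally would grade a child's event on the adult standard. No other passage in the article would direct that doctor elsewhere.

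What is at stake is the safety record of the younger participants. Under Data monitoring: Interim analysis, the monitoring board reviews the data every 6 months and is charged with protecting participants. If severity is part of what it sees, the article offers only this one standard for it. Grades that do not suit the participant's age would make that part of the record harder to interpret.

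**Working it through.** There is no figure in the plan to reproduce: the point depends on no rate, margin, power or sample size. The check is to set the passages side by side.

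**Inputs**

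| Item | What is stated | Where |
|---|---|---|
| Events covered | All, with no age limit | Harms |
| Severity standard | One, described as for adults | Harms |
| Minimum age | 8 years | Abstract; Eligibility criteria |
| Provision for minors | Assent at 8–17; caretakers join counselling under 18 | Ethical considerations; Adherence to interventions |
| Any paediatric scale or age-specific limit | None | Whole article |

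**Step 1. Do minors fall under the grading sentence?** Yes. They are eligible, the reporting rule covers all events, and the grading sentence makes no exception.

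**Step 2. Does the stated standard fit them?** Not as described. Its stated population is adults.

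**Step 3. Does the result depend on how the sentence is read?** There are two readings.

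- *Literal.* The system is an adult one. Events at ages 8–17 are then graded on adult criteria, and the sentence needs a paediatric counterpart.
- *Loose wording.* The cited system also has paediatric limits and the restriction to adults is a slip. The article then misdescribes its own standard, and a reader who follows it is pointed to adult criteria.

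The cited reference is not shown, so the documents cannot decide between the two. Both end in the same requirement: Harms has to be reconciled with Eligibility criteria and Ethical considerations.

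**Step 4. Can the effect be sized?** The number of misgraded events would be

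164 × (share aged 8–17) × (graded events per minor) × (proportion whose grade changes under age-appropriate criteria).

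Only the 164 is in the documents. The other three factors are not stated and cannot be derived, so no estimate is offered. Zero is not excluded.

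**The case against.** The strongest reply is that this is a three-sentence harms section in a condensed article. The full protocol and the operating procedures are not shown and may give the grading detail, and the cited system may already cover children. The second part stands as an uncertainty and is why the fix has two branches. The first part does not dispose of the point. The article is not silent on grading: it states a standard and states its population, and that population does not match its own eligibility rule.

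Several stronger readings are tempting, but the documents do not support them.

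- *Children's laboratory toxicity, creatinine for example, will be under-graded at every monthly panel.* Diagnosis and management of MDR-TB describes the blood count, liver and renal tests as routine care. No visible text says that these values are graded for the trial (Table 3 is not shown). The scale's cut-offs and paediatric ranges are not given either.
- *The effect can be counted.* Assuming that 3–10% of 164 are minors gives about 5 to 16 children (164 × 0.03 = 4.9; 164 × 0.10 = 16.4). One panel a month then gives 5 × 9 = 45 to 16 × 18 = 288 panels. The share has no basis in the documents, and the product counts panels, not misgraded events.
- *The safety comparison between arms is weakened.* Study outcomes lists no safety outcome, and the statistical sections specify no adverse event analysis by arm.
- *Misgrading would change who stops treatment.* No passage ties a grade to withdrawal, stopping or a board decision. Interventions: modifications leaves safety withdrawal to discretion without mentioning grade.
- *Stratifying by age group shows that children are treated as a separate group.* Without the cut-offs, the strata need not separate minors from adults.

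**Conclusion.** The point holds as a mismatch between a stated rule and the enrolled population. One severity standard, described as for adults, is applied to a trial that enrols from age 8, and nothing else in the article says how events under 18 are graded.

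Its size is unknown. The conclusion that children would be graded on adult criteria assumes that the Harms sentence is followed as written. It falls away if the cited system has paediatric limits and sites have used them; what then remains is a wrong description to correct. The point concerns safety grading only and leaves the adherence comparison, the non-inferiority test and the sample size untouched. It is worth correcting because it concerns the protection of minors and the remedy is small.

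**What to change.** Reconcile Harms with Eligibility criteria and Ethical considerations in one of two ways.

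1. If the cited system is for adults only, keep it for adults. State that participants under 18 are graded with age-appropriate (paediatric) severity criteria, with age-specific laboratory limits wherever laboratory values are graded.
2. If the cited system already contains paediatric limits, remove the restriction to adults and say that those limits apply under 18.

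In either case, check the grades already given to minors and correct them only where adult limits were used. Trial status reports enrolment at 70%, so some such grades may exist.

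The cost is one sentence, submitted through the amendment route described in Ethical considerations, plus a look-back at minors' events. The length of that look-back depends on the number of minors, which is not stated, and on whether the values needed were recorded. If laboratory values are graded, age-specific limits could be added to the out-of-range checks that Data management describes in the REDCap tool.
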